Chuna Manual Therapy (CMT) is a spinal manipulation technique based on the traditional Korean medicine (TKM) theory that both function and structure have systematic correlations. It is a therapeutic technique for modulating both orthopedic and functional balances simultaneously [15]. CMT usually involves high-velocity and low-amplitude thrusts to the joints and applies manual force to joints in the passive range of motion [16]. It is widely used in clinical practice for patients with musculoskeletal pain, such as low back pain, neck pain, or temporomandibular joint disorders [15]. A few clinical studies conducted in China have shown the efficacy of CMT or similar manual therapies for cervicogenic dizziness or vertigo. CMT has been compared with nimodipine administration [17], traction therapy [18], or combined treatment with acupuncture [19, 20], using randomized or nonrandomized designs. However, most of these interventions were carried out using muscle or tissue massage, which are not the similar techniques to Korean CMT spinal manipulation. Moreover, most of these studies assessed efficacy using invalidated response measures. Given the overall low quality of the studies and the differences in CMT techniques, there remains a need to rigorously demonstrate a clinical effect of CMT on cervicogenic dizziness.

The objective of this randomized controlled trial (RCT) is to test the efficacy and safety of 6-week CMT in male or female subjects, aged between 20 and 70 years, with cervicogenic dizziness, and compare them with the results from usual care (UC).

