### 2.1. Objectives and Hypothesis

This study is aimed primarily at exploring the therapeutic effect of adjuvant CMT for 6 weeks in male and female patients (20–70 years old) with cervicogenic dizziness, previously under usual care treatments. The null hypothesis is that the mean Dizziness Handicap Inventory (DHI) scores at baseline and at week 6 will be equal for the CMT and UC groups.

Second, the severity and frequency of cervicogenic dizziness after CMT or UC will be evaluated, along with other outcome measures. Differences between the two groups in neck pain, stress level, and quality of life (QoL) will also be assessed. The safety of CMT will be examined using adverse event (AE) reporting.

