### 2.14. Safety Assessment

AEs will be reported for every visit during the treatment period. The intensity and frequency of each event will be monitored. If serious AEs occur, postmanagement will be properly conducted. Local discomfort or pain, headache, fatigue, or referred pain can occur immediately after CMT but are usually mild and temporary.

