### 2.15. Sample Size Calculation

RCTs evaluating the efficacy of a manual therapy, compared with placebo, for cervicogenic dizziness gave values for the mean changes and standard deviations [11, 13]. With 15.9 as the mean difference between the intervention and control groups and 12.91 as the standard deviation, the necessary sample size calculated using PASS 14 was 12 per group (two-sided, *α* = 0.05 and 1 − *β* = 0.9). We will allocate a total of 50 participants (25 per group), allowing for an anticipated drop-out rate of 40%.

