### 2.16. Statistical Analysis

The full analysis set is defined as the group of participants who received CMT or UC and were assessed for the primary outcome at least once. The “per protocol” set is defined as the group of participants who completed all planned interventions and outcome assessments. Efficacy data will be analyzed primarily using the full analysis set and secondarily using the per protocol set. The missing data will be imputed using the “last observation carried forward” method. Safety data will be analyzed using the safety assessment set, which is defined as the group of participants who received CMT or UC at least once.

The primary and secondary outcomes will be statistically analyzed using two-sample *t*-tests or Wilcoxon's rank-sum tests for intergroup comparisons and paired *t*-tests or Wilcoxon's signed-rank tests for intragroup comparisons. Categorical variables from demographic data or AEs will be analyzed using the Chi-square test or Fisher's exact test.

An independent statistician ([name]) will analyze the data at *p* < 0.05 with SAS 9.4 software (SAS Institute Inc.).

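### With at most 25 per arm, a chi-square or Fisher test on adverse events at p < 0.05 says little about safety; section 2.16 should make estimates with confidence intervals the safety readout

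*Protocol article*

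**What the plan says.** The Introduction of the protocol article puts safety on a level with efficacy: "The objective of this randomized controlled trial (RCT) is to test the efficacy and safety of 6-week CMT", in comparison with usual care. Section 2.1 says how: "The safety of CMT will be examined using adverse event (AE) reporting". Section 2.14 has AEs reported at every visit and adds: "The intensity and frequency of each event will be monitored".

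Section 2.16 defines the safety set as "the group of participants who received CMT or UC at least once" and gives the between-arm analysis: "Categorical variables from demographic data or AEs will be analyzed using the Chi-square test or Fisher's exact test". It does not say when each of the two tests applies. The threshold is general: the statistician "will analyze the data at *p* < 0.05 with SAS 9.4 software".

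Section 2.15 derives the sample size from a DHI difference and standard deviation only, and concludes: "We will allocate a total of 50 participants (25 per group), allowing for an anticipated drop-out rate of 40" per cent. The article gives no expected AE rate, safety margin, safety hypothesis or power for safety.

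**The concern.** A significance test can show a difference between arms; failing to find one does not show that there is none. When the test has little power, a non-significant result is what one would expect both if Chuna Manual Therapy (CMT) adds no AEs and if it adds a moderate number. The p-value alone does not separate these cases.

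At stake is what the trial can say about safety at the end. Set against an objective of testing safety, a p-value above 0.05 could be reported as no difference in AEs although the data leave a sizeable excess open. An interval from the same data would show how large an excess remains compatible with them.

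**Working it through.** **Inputs from the protocol article.** 25 randomised per arm (2.15). The safety set keeps everyone treated at least once (2.16), so the anticipated 40% drop-out does not by itself shrink it, and 25 per arm is the maximum. Chi-square or Fisher's exact test at p < 0.05 (2.16), taken as two-sided, as in 2.15.

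**The plan's own figure.** There is none for safety. The 12 per group in 2.15 concerns the DHI and is not used here.

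**Assumed inputs.** The AE rates below are mine, shown as a range because the article gives none. The count 5/25 v 0/25 is likewise an illustration.

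**Step 1. One table, three p-values.** Take 5/25 v 0/25.

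- Fisher, two-sided: 2 × C(25,5) / C(50,5) = 2 × 53,130 / 2,118,760 = 0.0502.
- Uncorrected (Pearson) chi-square: 50 × (5×25 − 20×0)² / (25×25×5×45) = 781,250 / 140,625 = 5.56, p = 0.018.
- Yates-corrected: 50 × (125 − 25)² / 140,625 = 3.56, p = 0.059.

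The neighbouring tables:

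| Events | Fisher | Pearson | Yates |
|---|---|---|---|
| 4 v 0 | 0.110 | 0.037 | 0.118 |
| 5 v 0 | 0.0502 | 0.018 | 0.059 |
| 6 v 0 | 0.022 | 0.009 | 0.030 |

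At 4 v 0 and 5 v 0 the verdict depends on the test. At 5 v 0 the expected number of events is 2.5 per arm. The common convention (Fisher when an expected count is below 5) would select Fisher, but the article does not state it.

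**Step 2. Power.** Exact power is the sum, over all tables (a, b) with p < 0.05, of Bin(a; 25, p₁) × Bin(b; 25, p₂). The last column applies the convention above to each table.

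| Assumed AE rates | Fisher | Pearson | By convention |
|---|---|---|---|
| 20% v 5% | 20% | 38% | 22% |
| 20% v 10% | 9% | 17% | 11% |
| 30% v 10% | 30% | 45% | 41% |
| 40% v 20% | 23% | 35% | 35% |
| 30% v 5% | 55% | 71% | 61% |
| 40% v 10% | 59% | 73% | 72% |
| 40% v 5% | 82% | 91% | 88% |

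For excesses of 10 to 20 points, a real difference is more likely to be missed than found whichever test is used. At 25 to 30 points power runs from 55% to 73%. Only the 35-point excess exceeds 80% under every choice.

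**Step 3. What estimation would show.**

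- For 5/25 v 0/25 the risk difference is 20% − 0% = 20 points. The Newcombe 95% interval combines the Wilson limits of each arm (8.9% to 39.1%; 0% to 13.3%). Lower: 20 − √((20 − 8.9)² + 13.3²) ≈ 3. Upper: 20 + √((39.1 − 20)² + 0²) ≈ 39.
- For no events in 25, the exact two-sided 95% upper limit is 1 − 0.025^(1/25) = 13.7%.

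The first result is a visible signal that a bare Fisher p of 0.0502 would record as not significant. The second shows how little an event-free arm rules out.

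**The case against.** **The example is test-specific.** One might say that 5/25 v 0/25 is not significant under the plan. That holds for Fisher, by 0.0002, and for Yates, but not for the uncorrected chi-square, which the plan's wording also allows. The example shows dependence on an open choice, not a failure of both tests.

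**Power depends on assumed rates.** This stands. The article names local discomfort, pain, headache and fatigue after CMT as usually mild and temporary, and gives no rates. If such events were frequent with CMT and rare with usual care, say 40% v 5%, the test would probably find the difference. It would be wrong to say that a non-significant result is expected whatever harm CMT causes.

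**The test is not the whole safety assessment.** Also true. Sections 2.1 and 2.14 plan AE reporting at every visit, with intensity and frequency. A reader might infer that the authors mean to conclude safety from p > 0.05. The article does not say so: it has no margin, decision rule or sentence to that effect.

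**Estimates may be in the analysis plan.** They may, and the absence of table layouts from an article is no fault. The point concerns the method the article does state, which is a significance test. That any trial sized for efficacy has little power for AEs is a further reason not to rest the comparison on a p-value.

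**Conclusion.** The concern holds as a limitation of the stated method. Nothing in the text is contradictory or miscalculated, and testing AE categories by chi-square or Fisher is conventional. With at most 25 per arm, however, the test leaves excesses of 10 to 20 points undetected more often than not (power 9% to 45% across the tests and assumed rates shown), and close results such as 4 v 0 or 5 v 0 change verdict with an unspecified choice of test. A non-significant result would therefore not show that CMT is safe.

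The conclusion rests on 25 per arm being the maximum, on two-sided testing at 0.05, and on true AE rates within the range tabulated. It does not rest on any claim that the investigators intend to read p > 0.05 as safety.

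**What to change.** In section 2.16, make estimation the safety readout:

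1. In the safety set, report for each arm the number and percentage of participants with any AE and with any serious AE, each with an exact 95% confidence interval.
2. Report the between-arm risk difference with a 95% confidence interval, naming the method in advance (for example Newcombe), because interval and test methods can disagree in close cases.
3. Treat any p-value as supplementary, and fix which test produces it.
4. State that no safety conclusion will be drawn from p > 0.05, and that no events in 25 participants excludes only rates above about 14%.

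The cost is a change of wording and one table; AEs are already recorded at every visit, so no new data are needed. The downside is a more modest safety claim.

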## 3. Results and Discussion

This study protocol is for a prospective, pragmatic, assessor-blind, randomized controlled trial to test the efficacy and safety of TKM-based CMT in subjects with cervicogenic dizziness. Fifty participants will be randomly allocated to CMT or UC groups. Over 6 weeks, the CMT group will undergo 12 sessions of CMT, physical therapy, and patient education, whereas the UC group will undergo the same number of sessions of physical therapy and patient education. The primary outcome will be assessed as the change in a validated PRO, the DHI, between the baseline and closing time point. This is expected to be the first randomized controlled trial in Korea to perform CMT for cervicogenic dizziness. It is also meaningful to adopt CMT for neurological disorders, not just for musculoskeletal symptoms.

There are no CMT-specific recommendations for trial design, and few clinical trials of high quality have been published. We therefore followed the recommendations for acupuncture studies, or STRICTA [22], as much as possible. Because the CMT regimen consists of mandatory and discretionary techniques and the discretionary ones depend on the individual's condition, we strictly defined the qualifications required of CMT practitioners for this study and plan to document all CMT treatment decisions.

Another challenge was the screening process to identify eligible participants. As mentioned above, to diagnose cervicogenic dizziness, physicians must rule out other relevant disorders that can trigger dizziness [7]. Dizziness can arise not only from a variety of central or peripheral diseases but also from drug-related side effects. This was why we organized a research team with medical experts from various areas, including neurologists ([name] and [name]), ophthalmologists ([name] and [name]), physiatrists ([name] and [name]), and a medical methodologist ([name]). We intend to perform full examinations of the CNS and nystagmus, as well as extensive physical examinations and check-ups for medical history and concomitant medications. Cooperation and communication among the research teammates will be an essential factor toward a successful study.

## 4. Conclusion

We expect that this randomized controlled trial can provide a new complementary and alternative strategy to manage cervicogenic dizziness with adjuvant traditional manual therapy or CMT.

## Figures and Tables

**Figure 1 fig1:**
[figure not shown]
*Study flowchart*. CMT, Chuna Manual Therapy; CROM, cervical range of motion; DHI, Dizziness Handicap Inventory; EQ-5D, EuroQol Five-Dimension Questionnaire; GPE, global perceived effect; K-PSS, Korean version of Perceived Stress Scale; MVS, mean vertigo scale; NDI, neck disability index; PI-NRS, Pain Intensity Numerical Rating Scale; UC, usual care; VAS, visual analog scale.

**Table 1 tab1:** Study timetable.

	Screening	Randomization	Treatment							
Visits	V1	V2	V3	V4-V5	V6	V7	V8-V9	V10-V11	V12	V13
Time point	*−1 W*	*Day 0*	*1 W ± 2 D*	*2 W ± 2 D*	*3 W ± 2 D*		*4 W ± 2 D*	*5 W ± 2 D*	*6 W ± 2 D*	
**Enrollment:**										
*Informed consent*	×									
*Demographics *	×									
*Physical examination*	×									
*Vital signs*	×									
*Pregnancy test*	×									
*Medical history*	×									
*Concomitant medication*	×	×	×	×	×	×	×	×	×	×
*CNS examination*	×									
*Nystagmus examination*	×									
*Eligibility assessment*	×									
*Random allocation*		×								

**Interventions:**										
*CMT (twice/week)*										
*UC (twice/week)*										

**Assessments:**										
*DHI*	×	×				×				×
*MVS*		×				×				×
*VAS*		×				×				×
*Frequency*		×				×				×
*PI-NRS*		×				×				×
*NDI*		×				×				×
*CROM*		×				×				×
*GPE*										×
*K-PSS*		×				×				×
*EQ-5D*		×				×				×
*New BI*										×
*Adverse events*		×	×	×	×	×	×	×	×	×

BI, blinding index; CMT, Chuna Manual Therapy; CNS, central nervous system; CROM, cervical range of motion; DHI, Dizziness Handicap Inventory; EQ-5D, EuroQol Five-Dimension Questionnaire; GPE, global perceived effect; K-PSS, Korean version of Perceived Stress Scale; MVS, mean vertigo scale; NDI, neck disability index; PI-NRS, Pain Intensity Numerical Rating Scale; UC, usual care; V, visit; VAS, visual analog scale; W, week.

**Table 2 tab2:** CMT regimen for cervicogenic dizziness.

Regions	CMT techniques
Cervical spine	(i) Supine cervical distraction technique^*∗*^
	(ii) Supine cervical dysfunction correction technique^*∗*^
	(iii) Supine cervical dysfunction JS distraction/correction technique^*∗*^
	(iv) Prone cervical distraction technique

Thoracic spine	(i) Sitting upper thoracic dysfunction muscle release/strengthening technique (extension or flexion)
	(ii) Supine thoracic extension dysfunction correction technique
	(iii) Prone lower thoracic flexion dysfunction correction technique
	(iii) Sitting lower thoracic dysfunction muscle release/strengthening technique (extension or flexion)

Lumbar spine	(i) Prone lumbosacral distraction technique
	(ii) Sidelying lumbar rocking distraction technique
	(iii) Sidelying lumbar dysfunction correction technique (extension or flexion)
	(iv) Sitting lumbar flexion dysfunction muscle release/strengthening technique
	(v) Spine flexion distraction technique (flexion, extension, circumduction, sidebending, and magnum pump)

*Note*. The techniques marked by asterisks are mandatory, whereas the others are discretionary. The practitioners will evaluate each patient before the CMT sessions and perform individually necessary techniques to improve cervicogenic dizziness. CMT, Chuna Manual Therapy.

## Data Availability

The datasets generated and analyzed in this study will be available from the corresponding author upon reasonable request.

## Abbreviations

AE: Adverse event
CI: Confidence interval
CMT: Chuna Manual Therapy
DHI: Dizziness Handicap Inventory
UC: Usual care
MVS: Mean vertigo scale
VAS: Visual analog scale
PI-NRS: Pain Intensity Numerical Rating Scale
NDI: Neck disability index
CROM: Cervical range of motion
K-PSS: Korean version of Perceived Stress Scale
EQ-5D: EuroQol Five-Dimension Questionnaire
GPE: Global perceived effect
BI: Blinding index
TKM: Traditional Korean medicine
SPIRIT: Standard Protocol Items Recommendations for Interventional Trials
STRICTA: Standards for Reporting Interventions in Clinical Trials of Acupuncture
CNS: Central nervous system
NSAID: Nonsteroidal anti-inflammatory drug
PRO: Patient-rated outcome
QoL: Quality of life
RCT: Randomized controlled trial.
